## Abstract

**Background:**

Performing partial nephrectomy (PN) for suspected renal cell carcinoma (RCC) requires a careful clamping strategy to balance blood loss and postoperative kidney function. For better prediction of individual kidney perfusion, the proposed DIPLANN‐tool visualizes arterial perfusion zones using 3D models from CT scans to support surgeons in planning selective clamping (SC). We hypothesize that using 3D perfusion zone (3DPZ) models allows for more frequent and more accurate SC during robot‐assisted PN (RAPN). Furthermore, it might also benefit patients' health and insight.

**Study Design:**

PODRACING (Planning Operative strategy using a Digital Renal Artery ClampING tool) is a multicentre randomized controlled trial, evaluating the potential benefits of 3DPZ models. Patients will be randomized 1:1 to either the experimental group (DIPLANN‐tool + CT) or the control group (conventional CT alone).

**Endpoints:**

The primary endpoint entails planning and performing, as planned, an SC strategy. Key secondary endpoints include the performed clamping strategy (SC vs main artery clamping [MAC]) and the difference in kidney function at 6 months postoperative. Other secondary and exploratory outcomes include different aspects regarding patients' health, patients' insight and surgeons' benefits.

**Patients and Methods:**

All adult patients with cT1–2 N0 M0 renal cancer planned to undergo RAPN with multiphase CT scan with arterial phase available are eligible for inclusion. Apart from the availability of a 3DPZ model (during a preoperative study visit, while planning the surgical strategy and intraoperatively), study procedures are identical for the study group and control group. For the primary endpoint, the surgeon needs to lock his/her final clamping strategy on the study website. The surgeon can use his/her preferred operating method for RAPN (no limitations in surgical approach or robotic system) and postoperative hospitalization course. Postoperative visits entail visits at 1 month, 3 months, 6 months and 12 months.

**Registration:**

The trial is registered on ClinicalTrials.gov with identifier NCT06536439.^1^ The study was approved by the Belgian Federal Agency for Medicines and Health Products. Eudamed number: CIV‐23‐11‐044854.

## BACKGROUND

1

For patients diagnosed with localized kidney cancer, two main options exist to surgically remove the kidney tumour.^1^ During radical nephrectomy (RN), the entire kidney is removed. During partial nephrectomy (PN), only the tumour is resected, safeguarding the function of the remaining healthy kidney tissue. The latter procedure is generally preferred; however, not always technically feasible. To resect only the tumour, a balance has to be found in the clamping approach: clamping the blood supply to the kidney assures bloodless tumour resection, yet might compromise the postoperative renal function due to the temporary ischemia. Tumour resection without clamping, on the other hand, might lead to substantial blood loss. That is why ‘selective clamping’ (SC) is proposed. In this approach, only those selective arteries are clamped that perfuse the zone, including the tumour. The main drawback of this strategy is that it is often not clear which arteries should be clamped based on standard preoperative imaging, as misjudgement can lead to a high‐risk surgery with excessive bleeding in case incorrect SC is maintained or futile/risky renal arterial tree dissection is performed. Better prediction of individual kidney perfusion will allow for performing SC more accurately and thus possibly preserve healthier kidney tissue by less extensive ischemia.

With this project, we want to offer the surgeon an easy‐to‐use virtual planning tool that facilitates the decision‐making process regarding the feasibility of PN and the corresponding optimal clamping strategy. This tool uses virtual three‐dimensional (3D) models based on computed tomography (CT) scans to visualize precise information on the different anatomical structures and arterial perfusion zones. This may also improve patients' understanding of their own individual situation.^2^ In a technical validation study by De Backer & Vermijs, the proposed new tool (“Digital PLANning in partial Nephrectomy” = DIPLANN‐tool) demonstrated sufficient accuracy in 92% of patients when planning SC for robot‐assisted PN (RAPN).^3^ However, the tool's clinical added value still needs to be determined.

Our hypothesis entails that the 3D perfusion zone models in combination with conventional CT imaging, in patients diagnosed with localized kidney cancer who are planned to undergo renal cancer surgery, will improve patients' health, broaden patients' insight and facilitate surgical strategy planning, compared to conventional CT imaging alone.

In this report, we provide a detailed and comprehensive description of the PODRACING clinical trial protocol (Version 2.0, dd 20/11/2024), following the SPIRIT reporting guidelines.^4^ This includes an in‐depth overview of the study's overall design, the specific interventions being evaluated, the primary and secondary endpoints, as well as the planned methods for statistical analysis. The trial is registered on ClinicalTrials.gov with identifier NCT06536439.^5^ The study was approved by the Belgian Federal Agency for Medicines and Health Products. Eudamed number: CIV‐23‐11‐044854. A completed SPIRIT checklist is available as an additional file (Supporting Information).

## STUDY DESIGN

2

PODRACING (Planning Operative strategy using a Digital Renal Artery ClampING tool) is a confirmatory, multicentric, unblinded, randomized, controlled, pivotal trial using parallel group assignment and stratified randomization.

Patients will be randomized according to a 1:1 allocation ratio to either the experimental group (the DIPLANN‐tool in combination with conventional CT imaging) or the control group (conventional CT imaging alone), using permuted block randomization with blocks of varying size.

Randomization will be stratified by the following variables:Whether SC is deemed possible either according to the DIPLANN‐tool in combination with conventional CT imaging and/or according to conventional CT imaging only, as assessed by an independent surgeon (between inclusion and randomization) who will not be involved in the RAPN surgical procedure (yes vs no), see 5.2 ‘study procedures’ for more details.Hospital where surgery is performed (Ghent University Hospital vs AZ Maria Middelares Ghent vs AZORG Hospital Aalst vs AZ Sint‐Jan Bruges vs ZOL Genk).PADUA classification (low (<8) and intermediate (8–9) vs high‐risk (>9)). In case of multiple masses, the mass with the highest individual PADUA classification will be used.A static randomization list was developed by an independent statistician and uploaded in the randomization module of REDCap to allow for automated randomization.

The study will be rolled out in five high‐volume hospitals in Belgium (Ghent University Hospital, AZ Maria Middelares Ghent, AZORG Hospital Aalst, AZ Sint‐Jan Bruges and ZOL Genk), including surgeons with different ranges of experience in RAPN and in 3D modelling. We aim to randomize 235 patients diagnosed with localized kidney cancer who are planned to undergo renal cancer surgery.

## ENDPOINTS

3

An overview of the primary endpoint, as well as key secondary, safety and exploratory endpoints, is provided in Table 1.

**TABLE 1 bco270191-tbl-0001:** Overview of primary and secondary endpoints.

**Primary Endpoint**
Planning and performing as planned a SC strategy (considered by the surgeon at the end of surgery, objectified pre‐ and postoperatively through online assessment and controlled through video‐analysis by trained reviewers using predefined criteria)*
**Secondary Endpoints**
*Key Secondary Endpoints*
Change in eGFR at 6 months after surgery compared to eGFR preoperatively
Clamping strategy performed (SC or MAC)
*Secondary Endpoints*
Time to dissect hilum (minutes) as analysed on postoperative surgical video analysis
Conversion from SC to MAC
*Safety Endpoints*
Intra‐operative and 90‐day postoperative complications
Estimated blood loss during surgery (mL)
Concordance between the 3D perfusion model and peroperative kidney surface perfusion as visualized by indocyanine green (ICG) as estimated by postoperative surgical video analysis
*Exploratory Endpoints*
Patients' health
eGFR (CKD‐EPI) < 45 ml/min at 6 months after surgery
Change in eGFR (CKD‐EPI) after surgery at other time points up to 1 year (POD1, last measurement before discharge, postoperatively 1 month, 3 months, 12 months) compared to eGFR preoperatively
Ischemia time during surgery (seconds)
Positive surgical margin (PSM)
Robotic console time of surgery (minutes)
Length of hospital stay after surgery (days)
2 Patients’ insight
Quality of life (according to EORTC QLQ‐C30) up until 1 year after surgery (preoperatively, 3 months, 6 months, 12 months
Preoperative anxiety for surgery questionnaire (Hospital Anxiety and Depression Scale (HADS) + Symptom Distress Thermometer (SDT))
Preoperative patient knowledge questionnaire
3 Surgeon's decision
Time to dissect kidney (minutes)
Superselective clamping (yes/no)
% parenchyma rendered ischemic
Conversion from PN to RN
Time to prepare for surgery (minutes)

* For the primary objective, SC needs to be deemed possible either according to the DIPLANN‐tool in combination with conventional CT imaging or according to conventional CT imaging only, as assessed by an independent surgeon (between inclusion and randomization) who will not be involved in the RAPN surgical procedure, in order to be included in the analysis set. On the DIPLANN tool, SC is deemed feasible if ≥ 90% tumour ischemia and ≤ 70% renal parenchyma ischemia can be achieved. If these criteria are met, but it is technically or anatomically not feasible according to the independent surgeon to perform SC, he can deviate from these criteria and thus claim SC is not deemed possible. As a secondary objective, this endpoint will be analysed in the total study population.

The primary endpoint entails planning and performing, as planned, an SC strategy (considered by the surgeon at the end of surgery, objectified pre‐ and postoperatively through online assessment and controlled through video‐analysis by trained reviewers using predefined criteria). The surgical procedure of a patient is deemed to have a favourable outcome if an SC strategy is planned and performed as planned. A surgical procedure of a patient is considered to have an unfavourable outcome if main artery clamping (MAC) is planned, or if SC is planned, but cannot be performed as planned (other or adjusted SC is performed or MAC is performed). The primary endpoint will only be analysed in the subgroup of patients in whom SC is deemed possible (stratification factor, see ‘study procedures’). The secondary endpoints will be analysed for all patients.

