**ASSESSMENTS:**												
**Preoperative study visit explaining the procedure using either CT scan or 3D model**				x								
**Physical examination including height, weight, abdominal examination**				x								
**Blood examination including Hb, creatinine, eGFR**				x			x					
**Blood examination including creatinine, eGFR**								x	x	x	x	x
**Patient questionnaire regarding knowledge**				x								
**Hospital Anxiety and Depression Scale (HADS) + Symptom Distress Thermometer (SDT)**				x								
**EORTC QLQ‐C30 questionnaire**				x						x	x	x
**Online assessment by surgeon regarding selective arterial clamping information**					x							
**RAPN surgical procedure**						x						
**Postoperative questionnaire for the surgeon with surgical details and information on arterial clamping**						x						
**Histopathological examination of renal tumour**						x						
**Follow‐up consultations and monitoring of complications**									x	x	x	x

* Last measurement before discharge.

** Time window of 2 weeks before and 2 weeks after.

*** Time window of 4 weeks before and 4 weeks after.

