#### Subgroup analyses

5.9.5

To explore the heterogeneity of the primary estimand, subgroup analyses will be performed for the following subgroups:Hospital where surgery is performed (Ghent University Hospital vs AZ Maria Middelares Hospital vs other hospitals).Kidney function (eGFR < 30, [30–45[, [45–60[, ≥ 60).Highest individual PADUA classification (low (<8), intermediate (8–9) and high‐risk (>9)).

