#### Other analyses

5.9.9

Endpoints that are measured repeatedly will be analysed using generalized linear mixed models with a random intercept for patient, including time, arm, a two‐way interaction between time and arm and the stratification factors: whether SC is deemed possible, hospital, and the highest individual PADUA classification in the fixed effects part of the model.

Continuous endpoints measured at one point in time will be analysed using a linear regression model including arm and the stratification factors: whether SC is deemed possible, hospital and the highest individual PADUA classification. Log‐normally distributed endpoints will be log‐transformed before analysis.

Binary endpoints measured at one point in time will be analysed using a binary logistic regression model (with logit link function), including arm and the stratification factors: whether SC is deemed possible, hospital and the highest individual PADUA classification.

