#### Significance level and confidence intervals

5.9.11

The nominal type I error rate will be controlled at 5%. The hierarchy of endpoint families will be respected. Analysis of secondary endpoints will only be interpreted after demonstration of success on the primary estimand.

The interim analysis for the primary estimand will be performed at the 0.88% significance level and the final analysis at the 4.67% significance level (based on O'Brien Fleming group sequential boundaries).

Bonferroni correction for multiple testing due to multiple key secondary estimands will be applied, setting the significance level at 1.67%.

Subgroup analyses and analyses of other endpoints will be considered as exploratory and hypothesis‐generating.

Any deviation(s) from the original statistical analysis plan will be recorded as a note to file and reported in the final clinical investigation report and publication.

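### The exploratory endpoint of eGFR below 45 at 6 months ignores preoperative kidney function in its definition and its model, which costs precision but not validity (minor)

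*Protocol article*

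**What the plan says.** Table 1 (Exploratory Endpoints, Patients' health) defines the endpoint as "eGFR (CKD‐EPI) < 45 ml/min at 6 months after surgery". The two other eGFR endpoints in the table are changes from the preoperative value. One of them is the key secondary endpoint "Change in eGFR at 6 months after surgery compared to eGFR preoperatively".

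Table 2 contains no eGFR criterion for inclusion or exclusion. Section 5.9.5 plans subgroups by "Kidney function (eGFR < 30, [30–45[, [45–60[, ≥ 60", so patients below 45 before surgery are foreseen.

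For the analysis, Section 5.9.9 says: "Binary endpoints measured at one point in time will be analysed using a binary logistic regression model". The covariates are fixed as "including arm and the stratification factors: whether SC is deemed possible, hospital and the highest individual PADUA classification". Preoperative eGFR is not among them, and Section 2 does not stratify on it. It is measured: Table 3 schedules "Blood examination including Hb, creatinine, eGFR" at the preoperative visit.

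Section 5.9.11 sets the status of this analysis: "Subgroup analyses and analyses of other endpoints will be considered as exploratory and hypothesis‐generating".

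**The concern.** A patient who enters with eGFR below 45 and stays there is counted as an event, although surgery did not take that patient across the threshold. Among the others, crossing 45 depends largely on how far above it they started. The result therefore mixes existing with new impairment, and the stated model leaves out the variable that explains most of the variation.

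This is the only kidney endpoint in Table 1 expressed as a threshold for the individual patient, so readers are likely to take it as impairment after surgery. At stake are how it is read and how likely it is to show a real difference.

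**Working it through.** **1. The plan's own figures.** The article gives no event rate, effect size or power for this endpoint. The only planning figure used here is the total sample size, which reproduces: 202 / 0.86 = 234.9, so 235, allocated 1:1.

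**2. Assumed inputs (none are in the documents).**
- Preoperative eGFR: normal, with mean/SD of 85/18, 80/20, 75/22 or 70/22.
- Mean loss at 6 months, control versus tool: 10 versus 5, or 12 versus 4; 8 versus 8 for the null case.
- SD of individual change: 8, 12 or 16.
- Test: two-sided 5%, 2,000 simulated trials per setting, logistic regression on arm with and without preoperative eGFR. The stratification factors were left out at this step.

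**3. Share already below 45.** P = Φ((45 − mean)/SD):
- 85/18: Φ(−2.22) = 1.3%
- 80/20: Φ(−1.75) = 4.0%
- 75/22: Φ(−1.36) = 8.6%
- 70/22: Φ(−1.14) = 12.8%

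**4. Event rate, one setting checked by hand.** Mean 80, SD 20, control loss 12, SD of change 8: the 6-month value has mean 68 and SD √(400 + 64) = 21.5. So P(<45) = Φ(−23/21.5) = 14.3%, which matches the simulated 0.143.

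**5. Who the events are.** Across all settings, patients already below 45 supply 11 to 53% of events. Preoperative eGFR alone predicts the event with an AUC of 0.89 to 0.98.

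**6. Power without and with preoperative eGFR.** Relative loss = 1 − (without / with).

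| Mean/SD | Loss, control vs tool | SD of change | Without | With | Relative loss |
|---|---|---|---|---|---|
| 80/20 | 12 vs 4 | 8 | 0.362 | 0.718 | 50% |
| 75/22 | 12 vs 4 | 12 | 0.393 | 0.657 | 40% |
| 80/20 | 10 vs 5 | 16 | 0.143 | 0.197 | 27% |
| 70/22 | 10 vs 5 | 8 | 0.202 | 0.513 | 61% |

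The full range is 27 to 61%. By SD of change it is 45 to 61% (SD 8), 32 to 47% (SD 12) and 27 to 37% (SD 16).

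**7. With the Section 5.9.9 factors in the model** (frequencies assumed), power still rises in every setting with a tool effect: for example 0.36 to 0.57 (loss 1 − 0.36/0.57 = 37%), 0.41 to 0.82 (50%) and 0.17 to 0.23 (26%). Allowing for the uncertainty in all these inputs, a fair summary is very roughly one tenth to three fifths, mostly a quarter to a half.

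**8. Validity.** With no treatment effect, the rejection rate without the covariate is 0.036 to 0.057. Type I error is not inflated.

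**9. Restricting to patients at 45 or more.** Without the covariate, restriction changes power by only about −0.03 to +0.16. With the covariate, restriction lowers power in every setting with an effect (for example 0.718 to 0.687). At mean 80 it leaves about 16 to 23 events. The stated model has eight slopes if PADUA enters with three classes (arm 1, SC possible 1, hospital 4, PADUA 2), plus eGFR. With assumed factor frequencies, 17 to 37% of restricted fits fail or are unstable, against about 3 to 8% unrestricted.

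**The case against.** The endpoint is exploratory, carries no stated power, and supports no confirmatory claim. Surgery-related loss is already separated from existing impairment by the key secondary endpoint, whose mixed model in Section 5.9.7 includes the preoperative measurement. Status below 45 at 6 months is a legitimate description in its own right. Section 5.9.9 is a general default in a condensed article, and the unseen analysis plan may add covariates. The Discussion also notes that earlier studies did not show a clear renal benefit of selective clamping. With an assumed effect of 3 mL/min, power is about 9 to 11% without the covariate and 15 to 19% with it, so the endpoint would be weak either way.

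Most of this stands, and it makes the point minor. It does not remove the point: the article states a specific covariate list, and that list omits a strong predictor already in the data.

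A reader might infer more, but the documents do not support it:
- **That half the power is lost.** This holds under some assumptions, mainly when change varies little between patients. The documents give none of the inputs.
- **That 40 to 50% of events are pre-existing cases.** This is the upper part of a range of about 10 to 50%. Section 5.9.5 shows that such patients are foreseen, not how many.
- **That a patient below 45 is an event whatever the surgeon does.** With an assumed mean change of −2 and SD 10, about 17 to 20% of those starting below 45 finish at or above it.
- **That the result is biased.** Chance imbalance in preoperative eGFR adds noise, as with any unadjusted prognostic factor. Type I error stays near 5%.

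**Conclusion.** The point holds as a minor one. The definition takes no account of preoperative status, patients already below 45 can be enrolled, and the stated model omits a collected variable that is likely the strongest predictor. The comparison between arms remains valid. What is lost is precision, by the assumption-dependent range in step 7 of the working, and clarity about how much of the event count is new impairment. Nearly all of the recoverable power comes from the covariate; restricting the population helps interpretation only. The direction was the same in every setting with a tool effect. The size rests wholly on assumed eGFR distributions, losses and effects.

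**What to change.** For this endpoint, keep all randomised patients and add preoperative eGFR as a continuous covariate to the Section 5.9.9 logistic model. State that the odds ratio is then conditional on preoperative eGFR. Odds ratios are non-collapsible, and in one assumed setting the median estimate moved from about 0.50 to 0.17, so adjusted and unadjusted values must not be compared as if they were the same quantity. Alternatively, standardise the fitted model to a marginal risk difference, as Section 5.9.3 does for the primary endpoint.

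As a descriptive supplement only, report by arm the number with new eGFR below 45 at 6 months among those at 45 or more before surgery.

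The cost is a line or two in the analysis plan, settled before the data are analysed. No new data are needed, and the sample size and the confirmatory analyses are unaffected.

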## ELIGIBILITY CRITERIA

4

Inclusion and exclusion criteria are summarized in Table 2. We expect SC to be deemed possible (either according to the DIPLANN‐tool in combination with conventional CT imaging or according to conventional CT imaging only) in 202 of them (see sample size calculation under *Methods*) to assess our primary objective. No specific number of randomized patients per hospital is required.

**TABLE 2 bco270191-tbl-0002:** Inclusion and exclusion criteria for participation in the PODRACING trial.

**Inclusion criteria**
Aged 18 years or above
cT1–2 N0 M0 renal cancer
Planned to undergo RAPN
Multiphase CT scan with arterial phase available
Voluntary given and written informed consent
Proficiency in at least one of the study languages: Dutch, English, French
**Exclusion criteria**
> 3 ipsilateral renal masses
Women who are pregnant or breastfeeding
Previous renal surgery that is expected to complicate renal cancer surgery
cT ≥ 3
Planned off‐clamp resection
Cognitive disorder which impedes with completing study questionnaires

## METHODS

5

### Interventions

5.1

#### Description of the medical device

5.1.1

The medical device (DIPLANN‐tool) used in the study group is a software (name: DIPLANN – version: 2.0) that calculates the perfusion zones in the kidney and visualizes this information on a 3D model rendered in a web‐based environment (Figure 1). This information can be used by the surgeon to check for each renal arterial branch, which part of the tissue will become ischemic should it be clamped. Using this information, the surgeon can plan a surgical strategy (clamping strategy) and explain it visually to the patient.

